### 2.7 Study management

#### 2.7.1 Survey design phase

Prior to the official commencement of the study, a small-scale preliminary survey will be conducted. Based on the results of the preliminary survey and in conjunction with actual conditions, the recruitment and inclusion of research personnel will be refined, and the survey questionnaire will be perfected. Uniform professional training will be provided to all relevant research personnel to ensure the quality of the research work. This study follows the SPIRIT guidelines to ensure methodological rigor and transparency.

#### 2.7.2 Research implementation phase

The study will rigorously enforce the inclusion criteria for survey subjects, ensuring a meticulous selection and inclusion process into the study cohort. Participants with obesity pregnant women and their families will receive brochures detailing the prevention and treatment of chronic diseases, and informed consent will be obtained to ensure the authenticity of the feedback and to maintain a high response rate. Reminders will be sent via phone calls or text messages to minimize loss to follow-up during the survey process. Surveyors are committed to upholding principles of objectivity and equality, introducing the study's purpose and significance to each participant prior to commencing the survey and obtaining their informed consent. Furthermore, to ensure data integrity, the survey questionnaires will undergo regular review by auditors, with any inconsistencies or issues being addressed through immediate verification and correction.

#### 2.7.3 Data collection and analysis phase

In this study, we will utilize the “Wenjuanxing” (Questionnaire Star) online survey platform for questionnaire completion to ensure data accuracy. Before data analysis, we will conduct strict data organization and cleaning.

## 3 Discussion

The rising prevalence of obesity among Chinese pregnant women, as highlighted in the introduction (29). In a physical examination data based on 15.8 million adults, according to the Chinese standard (overweight BMI ≥ 24, obese BMI ≥ 28): the overweight rate is 34.8% and the obesity rate is 14.1%. Among the obese, 81.8% suffered from fatty liver, 36.9% had hypertension, and 42.4% had dyslipidemia (30). Consequently, there is an urgent need for healthcare interventions to both prevent and manage the development of obesity and its associated complications. Our study demonstrates that the AI-TLC intervention significantly improved maternal BMI and reduced adverse pregnancy outcomes compared to manual-only approaches. These findings align with prior research on technology-driven interventions. For instance, Ferrara et al. reported a 6-month BMI reduction of −0.9 ±1.5 in an mHealth-based intervention for gestational weight management (31), suggesting that digital tools can effectively support behavioral modifications. Similarly, our observation that the combined AI+Manual group outperformed standalone interventions echoes studies on hybrid models, where human-AI collaboration enhanced both adherence and personalization (23). Recent advances in AI interventions provide an appealing and cost-effective approach to intervention targeting the improvement of health outcomes for obese patients with other chronic disease comorbidity (30). To date, studies in Chinese obese patients with other chronic disease comorbidity have not been reported.

Our study introduces artificial intelligence driven therapeutic lifestyle changes (AI-TLC) intervention. The study aims to examine the effect of AI-TLC intervention on health behavior and health for obesity pregnant women. Several strengths warrant mentioning. Firstly, this study not only focuses on the treatment of obese individuals, but also considers obesity as a part of a pregnant women network and adopts multi-dimensional lifestyle modification as an intervention. This comprehensive intervention strategy is innovative in the management of obesity pregnant women. Secondly, an interdisciplinary team consisting of physicians, health managers, nutritionists, and artificial intelligence simulated health managers will be formed to provide comprehensive health management programs for obesity pregnant women. Thirdly, this study will introduce AI technology for health intervention to explore the application potential and effectiveness of AI intervention in obesity pregnant women management, which is prospective and innovative. Fourth, this study will conduct short-, medium- and long-term tracking and evaluation of the AI-TLC intervention effects, which will help to comprehensively understand the long-term impacts of the AI-TLC interventions and provide a basis for the development of sustained and effective health management strategies. Fifth, this study will evaluate the economic benefits of different interventions from a cost-benefit perspective and help to provide policymakers and healthcare providers with cost-effective intervention options.

Here are some extended comparisons with similar studies. The efficacy of AI-TLC interventions can be further contextualized by contrasting it with other obesity management strategies. Recent systematic reviews highlight that AI-driven interventions excel in providing real-time personalized feedback, a feature critical for sustaining behavioral changes in high-risk populations (32). For example, hybrid interventions combining digital tools and human support have shown superior long-term weight maintenance compared to purely automated systems, supporting our finding that the AI+Manual group achieved the highest clinical impact (33). This aligns with broader evidence that technology-enhanced programs improve accessibility in resource-limited settings (34), a key consideration for China's maternal healthcare system.

Next are the differences with the existing literature. Notably, our cost-benefit analysis revealed that the AI-only intervention offered a scalable solution with moderate efficacy, whereas the combined AI+Manual group achieved the highest clinical impact. This contrasts with Perdomo et al., who emphasized surgical and pharmacological interventions as primary strategies for severe obesity (15). However, our results align with Sallam et al., where TLC combined with medication synergistically improved metabolic outcomes (20). Such parallels suggest that hybrid models (AI + human expertise) may bridge the gap between resource-intensive and purely automated interventions.

However, this study has the following limitations. First, despite the high coverage rate of smartphones in China, some patients may not be able to use them well, which may hinder the implementation and reduce the effectiveness of AI interventions. Second, for the collection of the primary and secondary outcomes, we primarily used questionnaire indicators, which may inevitably lead to recall bias. Third, due to the lack of balanced stratification, comparative analyses between subgroups may not be suitable if the sample size of each group is insufficient across groups (e.g., compare the differences and potential influencing factors of AI-TLC intervention effects in different age groups). Fourth, the short-term follow-up period (up to 3 months postpartum) precludes conclusions about long-term weight maintenance. Meta-analyses of lifestyle interventions for obese pregnant women indicate that postpartum weight retention remains a challenge beyond 12 months (35), emphasizing the need for extended follow-up in future studies. Additionally, socioeconomic disparities in AI accessibility—particularly among older or rural populations—may limit generalizability, necessitating stratified analyses in broader cohorts.

Despite these limitations, this study may provide a scientific basis for developing personalized and effective interventions to further improve the health behavior and health of obesity pregnant women. It is expected to provide a new perspective and effective approach to the management of obesity pregnant women.

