In China, patients with obesity and chronic diseases face severe challenges. Internationally, interventions for patients with obesity and chronic diseases are often supported by professional medical teams and community health programs. In contrast, Chinese patients tend to rely on hospitals and themselves. In view of China, therapeutic lifestyle intervention combined with AI technology, as an innovative intervention, is easy to implement and cost-effective. Through AI technology, personalized lifestyle advice can be provided, monitoring patient health data and timely adjusting treatment options. This intervention not only facilitates patients to receive management at home, but also can deliver professional support to meet the needs of patients in the process of lifestyle change effectively and efficiently. Therefore, research targeting this area has important practical significance and urgency.

This study designed a randomized controlled study to propose an AI-driven therapeutic lifestyle change (AI-TLC) intervention. Through personalization, continuous tracking feedback, intelligent decision aid, evaluate the influence of AI-TLC intervention on health behavior and health outcomes of obese pregnant women, determine the applicability and universality of AI-TLC intervention, provide innovative, efficient, and personalized health intervention for obese pregnant women, and provide new perspectives and methods for related scientific research and clinical practice.

Specific objectives are:

Primary: Can the intervention program driven by artificial intelligence (AI)–facilitated therapeutic lifestyle changes effectively promote improvements in health behaviors and health outcomes among pregnant women who are overweight or obese?

Sub-question 1:

Do the effects of the intervention differ among pregnant women of varying ages and degrees of obesity?

Sub-question 2: From a cost-benefit perspective, which level of intervention is the most effective (human-only vs. AI-only vs. human + AI)?

Sub-question 3: What are the short-term, medium-term, and long-term effects of this intervention program? What mechanisms need to be added to achieve better long-term outcomes?

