## 2 Methods and analysis

### 2.1 Study participants and sample size

The baseline assessment for this study will be conducted at approximately 12 weeks of gestation. Follow-up visits are scheduled at approximately 20, 28, and 36 weeks of gestation, as well as at 3 months postpartum (24–32 weeks post-delivery). Figure 1 presents the detailed flowchart of this study.

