### 2.4 Outcomes

#### 2.4.1 Primary outcomes

The primary outcomes of the study include maternal body mass index (BMI), maternal weight, and adverse pregnancy outcomes. The primary outcome measures (such as BMI, maternal weight, and adverse pregnancy outcomes) will be assessed using Repeated Measures ANOVA or Mixed Effects Models to evaluate the intervention effects. For long-term effect analysis, Generalized Estimating Equations (GEE) or Cox Proportional Hazards Models will be employed to assess the short-term, medium-term, and long-term impacts of the interventions. Cost-effectiveness analysis will be conducted using Quality-Adjusted Life Years (QALY) and Incremental Cost-Effectiveness Ratios (ICER) to evaluate the economic efficiency of different intervention measures, with sensitivity analysis performed to verify the robustness of the results.

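### Sub-question 3, section 2.4.1 and the fourth strength promise long-term effects without qualification, but the stated follow-up cannot supply them for weight and BMI, and the follow-up times themselves disagree

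*Protocol article*

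**What the plan says.** Three places promise long-term results. Sub-question 3 in the Introduction asks "What are the short-term, medium-term, and long-term effects of this intervention program", and then what should be added to improve long-term outcomes. Section 2.4.1, under primary outcomes, states: "For long-term effect analysis, Generalized Estimating Equations (GEE) or Cox Proportional Hazards Models will be employed", the purpose being "to assess the short-term, medium-term, and long-term impacts of the interventions". In the Discussion, the fourth strength is that "this study will conduct short-, medium- and long-term tracking and evaluation of the AI-TLC intervention effects"; the authors expect a full picture of lasting impact from it.

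One place denies them for weight. The fourth limitation in the Discussion is that "the short-term follow-up period (up to 3 months postpartum) precludes conclusions about long-term weight maintenance". The sentence after it cites meta-analyses in which postpartum weight retention is still a problem past 12 months, and leaves longer follow-up to later research.

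The follow-up times are given in three further places:
- Section 2.1: "The baseline assessment for this study will be conducted at approximately 12 weeks of gestation", with visits at about 20, 28 and 36 weeks, "as well as at 3 months postpartum (24–32 weeks post-delivery").
- Section 2.5, Table 1: six columns, T-0 to T-5, with weight and BMI ticked in all six and no dates attached.
- Section 2.6: baseline and 3, 6 and 18 months as the time levels of the interaction with group.

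**The concern.** The same follow-up is presented as a strength because it is long-term and as a limitation because it is short-term. A limitation may properly qualify an objective, but here the objective, the planned analysis and the strength all stand unqualified, and none of the three excludes weight or BMI.

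No visit is assigned to the long-term horizon. An analyst who is asked for a long-term estimate and works from section 2.1 has only the postpartum visit to use. A report that labelled that visit long-term for weight or BMI would claim what the article's own limitation rules out. The second half of sub-question 3, on improving long-term outcomes, would rest on the same unobserved period.

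**Working it through.** The article gives no figure of its own to reproduce here. The check sets the statements on one time scale.

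**Inputs.** Baseline at about 12 weeks of gestation, and a last visit at 3 months or 24–32 weeks after delivery (section 2.1). An 18-month time point (section 2.6). Assumption, because the article gives no delivery date: delivery at 37–40 weeks of gestation. Conversion: 1 month = 365.25 / 12 / 7 = 4.348 weeks.

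**Step 1: the last visit, counted from delivery.**
- 3 months × 4.348 = 13.0 weeks.
- 24 / 4.348 = 5.5 months; 32 / 4.348 = 7.4 months.

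The label and its parenthesis in section 2.1 therefore disagree. Under either one there is a single postpartum visit, less than 7.5 months after delivery.

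**Step 2: the last visit, counted from baseline.**
- 3-month reading: (37 − 12) / 4.348 + 3 = 8.7 months, to (40 − 12) / 4.348 + 3 = 9.4 months.
- 24–32-week reading: (37 − 12 + 24) / 4.348 = 11.3 months, to (40 − 12 + 32) / 4.348 = 13.8 months.

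Neither reading reaches 18 months from baseline.

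**Step 3: where an 18-month point would fall.** Section 2.6 does not say from when it counts.
- From baseline: 18 − (40 − 12) / 4.348 = 11.6 months postpartum, to 18 − (37 − 12) / 4.348 = 12.3 months postpartum.
- From delivery: 18 months postpartum.

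Either would be well after the section 2.1 visit. No such visit is scheduled there, and the fourth limitation ends follow-up at 3 months postpartum.

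**Step 4: number of occasions.** Section 2.1 gives baseline + 3 antenatal visits + 1 postpartum visit = 5. Table 1 has 6 columns, so one collection point is undated. It could be a later visit. It could also be an early one, since section 2.2 describes an assessment before enrolment. The article does not say.

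**Step 5: what each statement supports.**

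| Place | Long-term data on weight and BMI? |
|---|---|
| Sub-question 3; 2.4.1; fourth strength | Promised |
| Section 2.1 | None later than 7.4 months after delivery |
| Fourth limitation | Ruled out |
| Table 1 | Undetermined: sixth column undated |
| Section 2.6 | Implied by an unscheduled 18-month point |

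Choosing one of the two dates in section 2.1 does not remove the contradiction with the limitation. Reconciling all the follow-up times could, if a later visit proves to be planned.

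**The case against.** The strongest reply is that the schedule is not settled. Section 2.6 has an 18-month point and Table 1 a sixth column. If a late visit is intended, the objective may be sound and the limitation may be the text in error. This stands, and it decides the form of the fix: a reader might infer that nothing will be observed after the section 2.1 visit, but that is true only of the section 2.1 schedule. It does not rescue the plan as written. The 18-month point appears in a sentence that contrasts intervention with control although the trial has three active arms, and both section 2.1 and the limitation contradict it.

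Second, the limitation concerns weight maintenance only. A reader might infer that the article rules out every long-term effect. It does not say so, and adverse pregnancy outcomes, also primary, are not a question of weight maintenance. All outcomes share the section 2.1 visits, so a wider limit is plausible, but it remains an inference.

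Third, a reader might take 12 months as the article's threshold for long-term. It is not: the figure appears only in a report of outside meta-analyses, and the article defines the term nowhere. For that reason the size of the gap is not expressed here as a share of 12 months.

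Fourth, the authors disclose the limit openly. That is to their credit, but it leaves the objective, the planned analysis and the claimed strength unchanged. Nor is this detail that an article may leave to a full protocol: the article states both sides itself.

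**Conclusion.** The contradiction is real, in a bounded form. Long-term effects are promised in three places without qualification, while the article calls its follow-up short-term and rules out conclusions on long-term weight maintenance. Under the section 2.1 schedule there is one postpartum visit, less than 7.5 months after delivery on either reading of its date, so the long-term part of sub-question 3 cannot be answered for weight and BMI.

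It would go too far to say that sub-question 3 as a whole is unanswerable: its short- and medium-term parts can be addressed at the scheduled visits. It would also go too far to treat the shorter schedule as established, because section 2.6 and Table 1 leave that open.

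The point affects what may be concluded. It shows no effect on sample size, error rates or the comparison of arms at the visits that are observed. The interval after delivery needs no assumption beyond the conversion of months to weeks; the figures counted from baseline, and the postpartum placing of an 18-month point counted from baseline, also assume delivery at 37–40 weeks. The change should be made before results are reported.

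**What to change.** First, reconcile the follow-up times in section 2.1, Table 1, section 2.6 and the fourth limitation. State the true last visit, give each of T-0 to T-5 a date, and say from when any point in months is counted.

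Then take the branch that applies.

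- **If the last visit is the postpartum visit in section 2.1:** in sub-question 3, section 2.4.1 and the fourth strength, replace the long-term wording with the horizons observed, namely 20, 28 and 36 weeks of gestation and the postpartum visit. State that no long-term effect on weight will be claimed. Mark the clause on better long-term outcomes as a question for later research, and remove the 18-month point from section 2.6.
- **If a later visit, such as one at 18 months, is really planned:** add it to section 2.1, define long-term by that visit, and correct the fourth limitation.

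The first branch costs wording only, and a less ambitious stated objective. The second also needs only text changes if the visit is already planned and resourced; this point does not ask for a new visit to be created.
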